### Data and safety monitoring

An independent Data and Safety Monitoring Board (DSMB) will be convened and will meet weekly for the first four weeks of the study and then monthly until database lock. The DSMB will monitor data completeness, duplication, rates of enrollment and participation, and the general study conduct. The DSMB will be composed of individuals with the appropriate expertise, including at least three independent clinicians and/or biostatisticians who, collectively, have experience in the management of biostatistics and the conduct and monitoring of randomized controlled trials. Members of the DSMB will be independent of trial conduct. The DSMB will review data from the treatment and control groups of the trial. At each meeting, a descriptive summary of withdrawals, serious adverse events and non-serious adverse events thought to be related to the study drug will be provided, along with outcome data for the primary outcomes. The DSMB will provide its input to the trial chief investigator.

Adverse events (AE) and adverse reactions (non-serious and serious) will be captured from the time of randomization until study day 29. For the purposes of this study, the investigator or delegate is responsible for recording all AE, regardless of their relationship to study treatment, with the following exceptions: (1) conditions that are pre-existing at enrollment and do not deteriorate; (2) abnormal laboratory values unless deemed clinically significant by the investigator and documented as such; (3) the onset of COVID-19 symptoms among asymptomatic household contacts or new symptoms within the household index case. The seriousness of an AE will be assessed by an investigator with the following exceptions: (1) elective surgery planned at the time of enrollment, and (2) hospitalization due to progression of disease will not be considered a serious adverse event (SAE) for the purposes of this trial.

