All adverse events/serious adverse events will have their relationship to the trial intervention and severity assessed by the investigator who evaluates the adverse event, based on temporal relationship and his/her clinical judgment. All severe adverse events will be reported immediately to the sponsor, except for those SAEs that are identified as not requiring immediate reporting. The immediate reports should be followed promptly by detailed, written reports. Clinic trial liability insurance will cover costs for participants who suffer harm during trial participation. Investigators will ensure harmed participants receive treatment for their condition.

IFN treatment is known to induce injection site erythema and, in up to 80% of recipients, an ‘influenza like’ syndrome, comprising fever, headache and body aches. Importantly, there are no respiratory signs or symptoms associated with IFN treatment, i.e. the response to IFN treatment is different than COVID-19 disease. However, ‘flu-like symptoms’ also occur in COVID-19 disease, and could lead to an increase in clinical tests in the IFN treated cohort if not appropriately managed. There are several strategies that may mitigate this potential response to IFN treatment that already constitute standard practice for multiple sclerosis (MS) patients on IFN therapy. Participants will be informed about the likely side effects of IFN treatment and asked to monitor and manage these. Monitoring consists of self-assessment of symptoms (there are no respiratory symptoms or anosmia known to be associated with IFN use) and the time frame during which this ‘influenza like’ syndrome following IFN treatment occurs (restricted to the first 4–24 h after administration of an IFN dose). Management consists of advising the participant to take acetaminnophen (provided to the participant) from the time of IFN administration up to 24 h after, to reduce the likelihood of this ‘influenza like’ syndrome. This approach is recommended for individuals with MS receiving IFN therapy (see PLEGRIDY package insert product monograph) and reduces syndrome symptoms by 80%.

Interferon ß-1a is safe when taken during pregnancy, with no evidence of increased rates of congenital anomalies or spontaneous abortions, according to data reported by the European IFNbeta Pregnancy Registry. If a female subject is diagnosed as pregnant by a positive.

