### Protocol modifications

Protocol modifications will be decided by consensus among members of the research investigator team to ensure successful completion of the trial and to minimize compromising the integrity of the trial. Changes will be reported to the Institutional Review Board, DSMB, and the Chilean Public Health Institute, who oversee the conduct of the trial. The full protocol will be available to the public upon request and approval by the investigators.

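### The immediate-reporting rule names severe events, but its exception names serious ones; 'severe' should read 'serious'

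*Protocol article*

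**What the plan says.** All of the relevant safety text is in the protocol article under Data and safety monitoring.

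- **Reporting rule:** "All severe adverse events will be reported immediately to the sponsor, except for those SAEs that are identified as not requiring immediate reporting". The next sentence adds the follow-up: "The immediate reports should be followed promptly by detailed, written reports".
- **Meaning of SAE:** hospitalization for disease progression "will not be considered a serious adverse event (SAE) for the purposes of this trial". The Abbreviations list expands SAE the same way.
- **Seriousness as a rating:** "The seriousness of an AE will be assessed by an investigator", with two exceptions (planned elective surgery and hospitalization for progression).
- **Severity as a rating:** adverse events, serious or not, have their relationship to the intervention and their "severity assessed by the investigator who evaluates the adverse event".
- **Parallel oversight:** the DSMB "will meet weekly for the first four weeks of the study and then monthly until database lock", and for every session "a descriptive summary of withdrawals, serious adverse events and non-serious adverse events thought to be related to the study drug will be provided". Its input goes to the trial chief investigator.

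**The concern.** Severity describes how intense an event is. Seriousness classifies its outcome or consequence. Expedited reporting normally follows seriousness, and the exception in this sentence is written as though it does. The rule itself is tied to severity.

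A serious event of moderate intensity is then outside the immediate report to the sponsor and the detailed report that follows. In the other direction, severe but non-serious reactions come in. The article expects an influenza-like syndrome in up to 80% of interferon recipients, so non-serious reactions will be common in that arm, although it does not say how many would be rated severe. Over-reporting of that kind is extra work; the safety gap is the missing serious events.

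**Working it through.** No arithmetic bears on whether the sentence is wrong. The check is a comparison of text.

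**Step 1: are the two words interchangeable here?** No. SAE is expanded as *serious* in the safety section and again in the Abbreviations. The sentence just before the rule has severity rated for adverse events and serious adverse events alike. A property graded within both groups cannot be the property that separates them. The article nowhere equates a severe event with an SAE.

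**Step 2: which events does the rule cover?**

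| Event | Rule as written | Rule with *serious* |
|---|---|---|
| Serious and severe | Immediate, unless exempt | Immediate, unless exempt |
| Serious, not severe | Not covered | Immediate, unless exempt |
| Severe, not serious | Immediate; the exception cannot apply | Not covered |
| Neither | Not covered | Not covered |

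The two versions differ in the two middle rows. As written, the exception can act only on the first row.

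**Step 3: does other text close the gap?** Only in part. Adverse events are recorded from randomization to day 29, apart from three listed exceptions, and serious events appear in each DSMB summary. That summary goes to a different body, on a meeting schedule, and the article does not say that it reaches the sponsor. No other sentence sets an immediate-reporting rule for serious events.

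**Step 4: what can be sized?**

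- *Events affected:* not derivable. The article gives no SAE rate and no breakdown of SAEs by severity.
- *DSMB interval:* up to 7 days between meetings in the first four weeks of the study, then up to about 31 days. Recruitment began in December 2020 and 251 households were enrolled at submission, so the weekly phase had very probably ended and the monthly interval is the relevant one. It shows when the DSMB would see an event; it does not measure the delay to the sponsor.
- *Households still to come at submission:* 310 − 251 = 59, and 59/310 = 19.0%, plus any then still in follow-up to day 29. This shows how far a correction could reach if the working protocol shares the error. It is not a measure of harm.

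**The case against.** The best defence is that the sentence corrects itself. The phrase introducing the exception points back to the events just named, so it reads naturally only if those events are SAEs. A reader would have to apply *severe* literally while ignoring the second half of the same sentence. The point about intent stands, and it is why this is graded as a slip. It does not make the stated rule right.

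A second defence is that the article condenses a full protocol, which field staff would actually follow. This also stands as far as it goes: the wording of that document is unknown, so no operational reporting failure can be claimed. Condensation explains what an article leaves out. It does not explain a stated rule that conflicts with its own exception.

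A third is that the affected class is narrow. Hospitalization for disease progression, an obvious source of hospital events in a COVID-19 trial, and planned elective surgery are already excluded from SAEs. What remains is events that are serious, not severe and not due to progression. That is fair and limits the likely consequence, though such events are the ones for which sponsor notification is of most use in judging the drug.

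Finally, no endpoint, estimand, sample size or analysis is affected. That is correct.

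**Conclusion.** The concern holds. The immediate-reporting sentence is wrong as written: its rule and its exception refer to different classifications, and taken literally it leaves serious events that are not rated severe out of the immediate sponsor report and its written follow-up.

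It is a minor inconsistency, worth correcting and almost certainly a drafting slip. Confidence is high for the wording. Nothing can be said about actual under-reporting, because that depends on the full protocol and on how staff apply the rule, neither of which is shown. No count of affected events can be given.

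**What to change.** Under Data and safety monitoring, change *severe* to *serious* in the reporting sentence and leave the exception as it stands. Rule and exception then refer to the same events, and severity remains a separate rating, as the preceding sentence already has it.

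In the article this costs one word. Check the full protocol for the same wording. If it is there, the change follows the route under Protocol modifications: consensus among the investigators, then notification ("Changes will be reported to the Institutional Review Board, DSMB, and the Chilean Public Health Institute"). No new data, visits or analyses are needed. If the full protocol already says *serious*, only the article needs correcting.

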### Treatment discontinuation, withdrawals, and loss to follow up

Participants may withdraw from the study at any time. Withdrawing from the trial will not affect their access to standard medical care. The treating medical team may also consider that continued participation is not in the best interest of the participant. In the case of discontinuation, the reason(s) for withdrawal will be documented. Consent to use study data, including data collected until the time of discontinuation and data to inform primary and secondary outcomes, will be requested specifically from participants. Following discontinuation, participants will receive standard care. Participants who withdraw will not be replaced.

### Protocol modifications

Protocol modifications will be decided by consensus among members of the research investigator team to ensure successful completion of the trial and to minimize compromising the integrity of the trial. Changes will be reported to the Institutional Review Board, DSMB, and the Chilean Public Health Institute, who oversee the conduct of the trial. The full protocol will be available to the public upon request and approval by the investigators.

### Data analyses

Analyses of data for primary and secondary objectives will be conducted per protocol and through intent-to-treat using the procedures detailed below and described in greater detail in a statistical analysis plan, available upon request. Data analysts will be blind to treatment allocation. Analyses will be conducted using R and statistical coding will be available to the public upon request and approval by the investigators.

#### Analysis for primary objective 1

The Primary Objective 1 is to determine whether IFNß-1a treatment reduces the number of COVID-19 cases still shedding SARS-COV-2 in saliva at day 11 following randomization. Statistical analysis of SARS-CoV-2 RT-PCR results from the index case population will be undertaken comparing IFN ß-1a treated index cases to index cases receiving only standard of care. A linear regression model (binomial family, logit link for dichotomous outcomes) will be applied to data collected, where a risk ratio (and 95% confidence interval) will be reported for the treatment arm variable, adjusted for age, sex, baseline viral load and vaccination status at enrollment.

#### Analysis for primary objective 2

The Primary Objective 2 is to determine whether IFN ß-1a treatment reduces the incidence of SARS-CoV-2 transmission from an index case to treatment-eligible household contacts, as measured by upper airway RT-PCR in contacts at day 11 after randomization. Statistical analysis of SARS-CoV-2 RT-PCR results from household contacts will be undertaken comparing households assigned to IFN ß-1a treatment or standard of care. A linear regression model (binomial family, logit link for dichotomous outcomes) with clustering within a household will be applied, where a risk ratio (and 95% confidence interval) will be reported for the treatment arm variable, adjusted for age, sex, baseline viral load of the index case, vaccination status of the index case, vaccination status of eligible contacts, contacts between index case and household contacts during the initial 11-day period, baseline RT-PCR and antibody levels of treatment eligible contacts at enrollment, number of household members and physical details of the household size, e.g. number of bathrooms, number of bedrooms.

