### Treatment assignment and randomization

Households will be randomized as clusters to receive either IFN ß-1a treatment or standard of care, once a household meets all the inclusion and none of the exclusion criteria. Households will be randomized to IFN ß-1a treatment or standard of care at a 1:1 ratio. The minimization technique (biased coin, *p* = 0.7) will be applied to achieve balance between groups stratified by the total number of people within the household. This will be implemented through a platform provided by the Telethon Kids Institute (https://qminim.telethonkids.org.au/).

Households will be randomized during the first home visit, once eligibility is confirmed, participants have signed informed consent, and baseline data collection procedures are completed. Field team members will contact the research laboratory, at which time the household assignment to treatment or standard of care will be made by the randomization software. Participants and study staff will not be blinded to randomization of treatment or standard of care, but all data analyses will be blinded to allocation.

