#### Secondary analyses

Additional analysis of both primary objectives will be conducted to include more rigorous group comparisons, e.g. Fisher’s exact test of proportions and a stratified Cochran-Mantel–Haenszel test of proportions. If the primary analysis method, the generalized linear model with binomial family and log link, does not fit the data well, or converge, a logit link will be used, meaning an adjusted odds ratio and 95% confidence interval will be reported. Specifically, a regression model will be used where the outcome variable is Yes/No for SARS-CoV-2 from the day 11 saliva specimen, with odds ratio and 95% confidence interval reported treatment (active/control) variable, following covariate adjustments. Primary objective 2 analysis will include clustering within households, where appropriate. Secondary outcomes will be reported and analyzed as above for the primary outcomes. Poisson and/or ordinal regression analysis will be conducted to compare days of viral shedding between the IFN treated and standard of care groups. The Cox proportional hazards regression model, with similar adjustments for variables as above, will be employed to examine time based, and specifically time-censored, outcome variables between groups. In addition, Bayesian analyses will be estimated using data-generated distributions of viral shedding at days 11, 16, and 29, and household infection rates. These prior distributions will be used to generate posterior probabilities for the intervention arm.

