### Sample size and power considerations

Three hundred and ten households will be randomized to treatment or standard of care. Households will be randomized as clusters, assuming 4 individuals per household; approximately 1240 individuals will be enrolled. Data from Wuhan, China, suggest the proportion of untreated index cases still shedding virus at day 11 is ~ 85% [22]. A sample of 278 households (310 considering a 10% drop out rate) has > 90% power, at alpha 0.025, to detect a difference between the proportion of index cases shedding virus at day 11 between the treatment arm and standard of care arm, if the proportion is 65% in the treatment arm; based on a two-tailed Fisher’s exact test. In addition, the sample, including 834 household contacts (417 per arm), has > 90% power, at alpha 0.025, to detect an odds ratio of 0.5 for a reduction in transmission to a household contact; based on a two-tailed stratified Cochran-Mantel–Haenszel test, with intra-class correlation 0.15.

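### Both primary models pair a logit link with a risk ratio, the next section names a log link as primary, and the fallback switches from risk ratio to odds ratio without a stated fit criterion

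*Protocol article*

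**What the plan says.** Under Data analyses, the model for primary objective 1 is called a linear regression with "binomial family, logit link for dichotomous outcomes) will be applied to data collected, where a risk ratio (and 95% confidence interval) will be reported" for treatment arm, adjusted for age, sex, baseline viral load and vaccination status. Objective 2 repeats the pairing: "A linear regression model (binomial family, logit link for dichotomous outcomes) with clustering within a household will be applied, where a risk ratio". Its longer covariate list includes the number of household members and contacts between index case and household contacts over the first 11 days.

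Under Secondary analyses the primary method is described differently: "If the primary analysis method, the generalized linear model with binomial family and log link, does not fit the data well, or converge", then "a logit link will be used, meaning an adjusted odds ratio and 95% confidence interval will be reported".

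The planning rates for objective 1 are in Sample size and power considerations: "the proportion of untreated index cases still shedding virus at day 11 is ~ 85" per cent, with 90% power "if the proportion is 65% in the treatment arm; based on a two-tailed Fisher’s exact test". The target effect for objective 2 is an odds ratio of 0.5, with no control transmission rate given.

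**The concern.** There are two faults.

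- **The primary model is contradictory.** The treatment coefficient of a binomial model estimates a log odds ratio under a logit link and a log risk ratio under a log link. Data analyses joins the logit link to the risk ratio, for both co-primaries. Secondary analyses makes the log link primary and equates the logit link with an odds ratio. No step is described that would turn the logistic fit into a risk ratio.
- **The fallback changes what is reported.** If the log-link model is judged to fit badly or does not converge, the headline result becomes an odds ratio. Convergence and fit are known only once the model has been run, and no threshold for adequate fit is given. Two analysts with the same data could report different measures, each within the plan.

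At stake is the meaning of the main effect estimate. For a common outcome an odds ratio lies much further from 1 than the risk ratio for the same data, and readers often take one for the other.

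**Working it through.** **Inputs.** From Sample size and power considerations: control 85%, treatment 65%, 278 evaluable households, alpha 0.025 two-sided, 10% drop-out. Allocation is 1:1, so 139 index cases per arm.

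**The plan's own figure.** Exact enumeration of Fisher's test at 139 per arm gives 93.9% power (normal approximation 95.1%), which agrees with the stated figure of more than 90%. Drop-out: 278 / 0.9 = 309, against 310 stated. These figures do not depend on the link and are not in question.

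**Objective 1, the two measures at the planning rates.**
- Risk ratio = 0.65 / 0.85 = 0.765; relative reduction 1 − 0.765 = 0.235, about 24%.
- Odds ratio = (0.65/0.35) / (0.85/0.15) = 1.857 / 5.667 = 0.328; 1 − 0.328 = 0.672, about 67%.
- SE of log risk ratio = √[0.35/(0.65×139) + 0.15/(0.85×139)] = 0.072; unadjusted 95% CI 0.66 to 0.88, z = −3.74.
- SE of log odds ratio = √[1/(139×0.65×0.35) + 1/(139×0.85×0.15)] = 0.297; unadjusted 95% CI 0.18 to 0.59, z = −3.76.

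The z values are nearly equal. Unadjusted, the choice of link hardly alters the test of no effect; it alters the size of the reported effect.

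**Objective 2.** With control risk p, RR = OR / (1 − p + p×OR). Since p is not given, it is assumed over a range, with OR = 0.5:

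| Assumed control risk | Risk ratio |
|---|---|
| 10% | 0.5/0.95 = 0.53 |
| 20% | 0.5/0.90 = 0.56 |
| 30% | 0.5/0.85 = 0.59 |
| 50% | 0.5/0.75 = 0.67 |

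**How likely is the fallback for objective 1?** The documents give no covariate effects, so any rate is illustrative.
- One simulation used 278 index cases, logistic truth set to give roughly 85% and 65%, and log-odds effects of 0.2 per SD of age, −0.3 for vaccination and 0.3, 0.7 or 1.0 per SD of viral load (300 runs each). The adjusted log-link fit failed to converge, or gave a fitted risk of 1 or more, in 89%, 100% and 100% of runs.
- In the same runs the risk ratio standardised from the logistic model had median 0.76 throughout, while the median adjusted odds ratio went from 0.31 to 0.26.
- A different criterion (constrained maximum likelihood, solution on the boundary, 150 datasets per setting) gave 39% with no covariate effects and 97% with moderate ones.

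The switch is therefore plausible, but its frequency depends on the assumed effects and the fitting algorithm. A boundary solution is also not identical to the protocol's own trigger.

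**The case against.** The best defence is that Data analyses contains a slip, logit for log. Read that way, it agrees with Secondary analyses: log link, risk ratio, and a logit fallback reported openly as an odds ratio. The authors clearly know the difference between the measures, the fallback is set down beforehand, and analysts are stated to be blind to allocation.

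Much of this stands. A reader might infer that the trial will publish an odds ratio under the name of a risk ratio. The documents do not support that: it would happen only if Data analyses were followed literally and the logit coefficient exponentiated, whereas Secondary analyses labels the logit result correctly. A reader might also infer that the measure will be chosen after the results are known. That is not supported either; the switch is pre-written, and what is missing is a criterion for fit.

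The defence does not remove the fault. The logit and risk ratio pairing occurs twice, so the text itself does not settle which section is in error. Correcting the slip would still leave a primary measure that depends on how the model behaves. A risk ratio can be derived from a logistic model by standardisation, but no such step appears. The analysis plan, which is not shown, may add detail; the contradiction in the published text would still need correcting.

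**Conclusion.** The point holds and should be corrected before allocation is revealed to the analysts. As written, the primary effect measure is not uniquely defined for either co-primary.

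The numerical consequence is established for objective 1 only, and rests on the protocol's own 85% and 65%. The same size should not be read across to objective 2: that gap turns on the unstated control risk, with 0.5 against 0.53 at an assumed 10% and 0.5 against 0.67 at an assumed 50%. Nor is failure of the log-link model a certainty; an outcome near 85% with continuous covariates such as age and baseline viral load makes it a realistic event, and no stronger statement can be drawn from the documents.

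**What to change.** Make the two sections agree on one primary effect measure for both co-primaries, the adjusted risk ratio, and drop the term linear regression. Choose one method that always yields that measure, and give it a fallback that does too:

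- **Logistic regression with marginal standardisation** over baseline covariates. Use a delta-method or bootstrap interval for objective 1, and a household bootstrap or cluster-robust interval for objective 2. Leave contacts during the 11-day period out of the objective 2 model: they arise after randomisation, and standardising over them would not in general give the total effect of treatment.
- **Modified Poisson regression** with robust standard errors for objective 1 and household-cluster-robust standard errors for objective 2.

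These are alternatives resting on different mean models and need not give the same number, so one must be named in advance. Remove the switch to the odds ratio and report the odds ratio as supplementary only.

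A separate and minor improvement: the minimisation seeks "balance between groups stratified by the total number of people within the household", and household size is in the objective 2 model but not in that for objective 1. Adding it there costs nothing.

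The whole change needs wording and a few lines of R, with no new data and no change to the sample size.

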### Primary and secondary objectives

The two co-primary objectives of this study are:To determine whether IFN ß-1a treatment reduces the proportion of infected cases shedding SARS-CoV-2 at day 11 after randomization.To determine whether IFN ß-1a treatment reduces the incidence of SARS-CoV-2 transmission from index cases to treatment-eligible household contacts, as measured by any positive upper airway infection evidenced by real-time Polymerase Chain Reaction (RT-PCR), in contacts at day 11 after randomization.

Secondary objectives of this study are:To determine whether in index cases infected with SARS-CoV-2, IFN ß-1a treatment compared with standard of care reduces the duration of SARS-CoV-2 upper airway virus shedding over 28 days following randomization.To determine whether IFN ß-1a treatment affects the incidence of SARS-CoV-2 upper airway infection or serological conversion by study day 29 in household contacts.To determine whether IFN ß-1a treatment compared with standard of care reduces the proportion of infected cases that require hospital admission or die due to COVID-19.To determine the safety of IFN ß-1a in the treatment and prevention of SARS-CoV-2 infection.

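### Each co-primary is sized at two-sided alpha 0.025 but reported with a 95% interval in two unranked analysis sets, so the level and the set that decide success need stating

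*Protocol article*

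**What the plan says.** The objectives section opens its list with "The two co-primary objectives of this study are": shedding in infected cases at day 11, and transmission to treatment-eligible household contacts by day 11. It does not say whether one or both must be met.

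Sample size and power considerations gives the same level to each. For index cases the sample "has > 90% power, at alpha 0.025, to detect a difference between the proportion of index cases shedding virus at day 11". For contacts it "has > 90% power, at alpha 0.025, to detect an odds ratio of 0.5 for a reduction in transmission to a household contact". Both calculations use two-tailed tests: Fisher's exact test for index cases, and for contacts a stratified Cochran-Mantel-Haenszel test that allows for an intra-class correlation of 0.15.

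Data analyses does not mention 0.025. For each of the two primary models it specifies an analysis "where a risk ratio (and 95% confidence interval) will be reported for the treatment arm variable". The Secondary analyses subsection keeps 95% for the fallback odds ratio. It also lists Fisher's exact test and a stratified Cochran-Mantel-Haenszel test as additional comparisons for both primary objectives.

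On analysis sets, the section says the primary and secondary analyses "will be conducted per protocol and through intent-to-treat". Management of missing data speaks of including all participants so as to comply with ITT, but it does not rank the two sets. A separate statistical analysis plan is mentioned as available on request; it is not at hand.

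**The concern.** An alpha of 0.025 for each of two objectives is what one uses when either may be claimed alone and the overall error is to stay at 0.05. The interval that goes with that level is 97.5%. The article sizes at one level and reports at another, with nothing to connect them.

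Readers of a trial report commonly take a 95% interval for a risk ratio that excludes 1 as a positive result. If that happens here, a co-primary with a p-value between 0.025 and 0.05 would be presented as a success although it fails at the level used for sizing. Having two analysis sets with no stated priority gives each objective a second route to a positive result. That is a separate and smaller problem than the interval level.

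**Working it through.** **Inputs from the article.** Two co-primaries; alpha 0.025 each, two-tailed; 278 evaluable households at 1:1, so 139 per arm; 85% against 65% shedding at day 11; 834 contacts, 417 per arm; intra-class correlation 0.15; 95% intervals for the primary and fallback models; two analysis sets.

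**The plan's own figure.** Exact enumeration of the two-sided Fisher test with 139 per arm and 0.85 against 0.65 gives:

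- at alpha 0.025: power 93.9%, which reproduces the stated > 90%;
- at alpha 0.05: power 96.7%.

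Both exceed 90%, so the power statement cannot show which level the analysis is meant to use. For dropout, 278 / 0.90 = 308.9, or 309, against the stated 310; this is immaterial.

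**Level of the interval.** Two-sided 0.05 has critical value 1.960 and matches a 95% interval. Two-sided 0.025 has critical value 2.241 and matches a 97.5% interval. The ratio of widths on the log scale is 2.2414 / 1.9600 = 1.144.

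**Family-wise error if either co-primary may be claimed.**

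| Level per co-primary | Independent endpoints | Upper bound |
|---|---|---|
| 0.025 (as sized) | 1 − 0.975² = 0.0494 | 0.025 + 0.025 = 0.05 |
| 0.05 (95% intervals decide) | 1 − 0.95² = 0.0975 | 0.05 + 0.05 = 0.10 |

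The ratio is 0.0975 / 0.0494 = 1.97, so about 2. A simulation with an assumed correlation of 0.3 between the two endpoints gives about 0.095 in place of 0.0975, so dependence of that size changes little.

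**Adding the second analysis set.** The article gives no overlap between the sets, so the correlation between the ITT and per-protocol test statistics is an assumption. Simulated with independent endpoints, counting a win in either set:

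| Assumed ITT/per-protocol correlation | 0.025 per test | 0.05 per test |
|---|---|---|
| 0.98 | 0.059 | 0.115 |
| 0.95 | 0.065 | 0.125 |
| 0.90 | 0.071 | 0.136 |

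The doubling therefore comes from the interval level alone. The unranked sets add roughly 0.02 to 0.04 at 0.05 per test. With 97.5% intervals they would still take the total slightly above 0.05.

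**Does holding to 0.025 cost power?** Objective 1 stays at 93.9% (unadjusted Fisher test). For objective 2 there are 834 / 278 = 3 contacts per household, a design effect of 1 + 2 × 0.15 = 1.3 and an effective 417 / 1.3 = 320.8 per arm. The control attack rate is not stated. Under assumed rates of 20%, 25%, 30% and 40%, power for an odds ratio of 0.5 at 0.025 is about 81%, 88%, 93% and 97% (normal approximation). Whatever the true rate, the stated power was claimed at 0.025, so testing at 0.025 takes nothing away from the plan.

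**The case against.** The strongest reply is that the article only says a 95% interval will be reported. It nowhere says that an interval excluding 1 means success. A 95% interval for estimation can sit beside a test at 0.025, and 0.025 is the only error level the article names. The interval is not the only inferential output either: Fisher's test and the Cochran-Mantel-Haenszel test, the two tests used for sizing, appear among the additional analyses. An article may leave the decision rule to the full analysis plan.

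Much of this stands. A reader might infer that claims will be made at twice the planned error rate; the documents do not support that, because no decision rule is given. What remains is a difference on the page: the sizing fixes 0.025, while the primary and fallback models fix 95%. The two sized tests are labelled additional, so they do not settle which result decides.

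That either objective may be claimed alone is also an inference. If both had to succeed, 95% intervals would cause no inflation above 0.05. But the split to 0.025 would then be unnecessary, so one sufficing is the likelier reading. Reading 0.025 as a per-tail level would match 95% intervals, but the article ties it to two-tailed tests.

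On the analysis sets, the missing-data text leans towards ITT without ranking it. A reader might also infer that per-protocol exclusions would fall mainly in the interferon arm, since controls have no injections to miss. The article does not support this. It gives no per-protocol definition, it says staff administration will secure adherence, and control participants can also depart from protocol, for example by taking another investigational treatment or leaving the household.

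**Conclusion.** The point holds as a mismatch between design and reporting, not as a demonstrated error in the conclusions. Sizing uses two-sided 0.025 per co-primary; the primary analyses specify 95% intervals in two sets with no stated priority. If those intervals judge success and either objective may be claimed alone, the family-wise error is 0.0975 under independence, at most 0.10, against a planned 0.05. If a win in either set also counted, it would be about 0.115 to 0.136 for assumed correlations of 0.98 to 0.90. If both objectives must succeed, or if a test at 0.025 in one named set decides, there is no inflation. The article does not say which of these applies. It is worth correcting because the remedy is a few sentences. At manuscript submission 251 of 310 households had been enrolled, so the rule could still be fixed before the final analysis.

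**What to change.** In Data analyses, including the Secondary analyses subsection:

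1. State that each co-primary is tested at two-sided 0.025 on the primary adjusted model, and that either may be claimed alone (or that both are required, if that is the intention).
2. Report 97.5% intervals for the two co-primary effects, including the fallback odds ratio. 95% intervals may stay for all other outcomes, or be added for the co-primaries if labelled descriptive.
3. Name ITT, with all randomised households, as the confirmatory set and per-protocol as sensitivity.
4. Say that the additional Fisher and Cochran-Mantel-Haenszel tests are supportive and do not decide.

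A step-down rule such as Holm is not needed. It would allow the second objective to be tested at 0.05, which would not match a 97.5% interval and would bring back the same kind of mismatch.

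The cost is wording and co-primary intervals about 14% wider on the log scale. The sample size does not change, because 0.025 is the level already used for sizing. The change should be dated before allocation is revealed to the analysts.
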